### 2.6 Randomization and blinding

A random number table will be generated using a computerized random number generator program. The resulting random allocations will be placed into opaque envelopes labeled with sequential study numbers. Two sets of these envelopes will be created: one for randomization at the site and another stored in the investigator’s office for emergency unblinding purposes. Each participant will be assigned a sequential study number, and an independent research staff member will prepare the corresponding α-mangostin hydrogel film or placebo film according to the random allocation sequence. Throughout the study, both study participants and outcome assessors will be kept unaware of the allocated intervention to maintain blinding.

### 2.7 Outcomes

Ulcer pain score, ulcer diameter and adverse event will be assessed as the outcome measurements. Ulcer pain score will be measured once a day using Visual Analog Scale (VAS) pain record individually by the participants. Ulcer diameter will be measured in the first, third, fifth, and seventh day of the study by the outcome assessors. Adverse events (AEs) will be documented once participants commence drug administration. The AE record will encompass: descriptive analysis, the timing of onset and resolution, severity, frequency, the necessity for treatment, and, if administered, the details of the treatment provided. Vital signs, including body temperature, respiratory rate, heart rate, and blood pressure, will be monitored during follow-up visits. Additionally, participants will also be queried about any discomfort symptoms they may be experiencing.

### 2.8 Intervention

Participants will receive the α-mangostin hydrogel films with a chitosan-alginate base or a placebo hydrogel film for 7 days. Application occurs according to the following directions (Figure 1):

**FIGURE 1 F1:**
[figure not shown]
Flowchart of study protocol.

Patients in group 1 will receive α-mangostin hydrogel films with a chitosan-alginate base in the form of a patch. Each patch consists of 0.25 mg α-mangostin, 2% of alginate sodium, 0.2% of chitosan, 1% of glycerin, pure ethanol, and aquades. The patch is applied to the affected oral area twice daily (after breakfast and dinner) for a duration of 1 h. The patients will be advised to refrain from eating and drinking during patch application for up to 1 h post-application. In the event of a missed application of the test substance, participants are encouraged to apply the patch as soon as possible. However, if it is approaching the time for the second evening application, participant should skip the initial dose, and proceed to apply the second patch after dinner as scheduled. Participants are required to notify the researcher during evaluation and monitoring if such deviations occur. The supervision of therapy application by a pharmacist acting as the principal investigator is integral to this process.

Patients in group 2 will receive the placebo film with the same materials but without active ingredient or α-mangostin and apply with the same instructions that were provided to group 1.

The use of mouthwash, antihistamines, immunosuppressive agents, antibiotics, and analgesics is strictly prohibited during the clinical efficacy trial period. Visual analog scale records and sheets for noting side effects/adverse drug reactions are provided throughout the testing phase. Participants are instructed to record pain scores daily during the ulcerative stage and to document any side effects associated with the film usage. Ulcer size is documented on days 1 (baseline), third, fifth, and seventh. Record sheets and any remaining hydrogel film are collected at the end of the study. Participants are directed to promptly discontinue film usage if rash or oral mucositis appears during the trial and report any occurrences to the supervising physician and researcher.

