## Abstract

**Background:** Recurrent Aphthous Stomatitis (RAS) is a common ulcerative disease of the oral mucosa which is characterized by pain, and recurrent lesions in the oral cavity. This condition is quite painful, causing difficulty in eating, speaking and swallowing. Topical medications have been used for this condition, but the obstacle in using topical medications is the difficulty of achieving drug effects due to saliva wash out. This problem can be overcome by film hydrogel formulation which can protect the ulcer and reduce the pain to some extent. α-mangostin is a xanthone isolated from the rind of the mangosteen fruit. One of the activities of α-mangostin is anti-inflammatory effects, which operate through the characteristic mechanism of inhibiting the inflammatory response. This protocol study aims to investigate the efficacy of an α-mangostin hydrogel film with a chitosan alginate base for recurrent aphthous stomatitis (RAS) in comparison with a placebo over a period of 7 days.

**Study design:** This is a two-arm, double blinding, randomized controlled trial enrolling patients with RAS. The efficacy test of α-mangostin Hydrogel Film will be tested against the placebo. Patients with RAS will be allocated randomly into the two arms and the hydrogel film will be administered for 7 days. The diameter of ulcer and visual analog scale (VAS) score will be used as the primary efficacy endpoint. The outcome measure will be compared between the two arms at the baseline, day 3, day 5, and at the end of 7 days.

**Discussion:** The purpose of this clinical research is to provide scientific evidence on the efficacy of α-mangostin hydrogel film with a chitosan alginate basis in treating recurrent aphthous stomatitis. The trial is expected to improve our capacity to scientifically confirm the anti-inflammatory effectiveness of α-mangostin compounds in a final formulation that is ready to use.

**Trial registration:** NCT06039774 (14 September 2023).

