### 2.9 Statistical analysis

All data will be analyzed using the Independent Samples *t*-test model in SPSS Version 26 to compare age, time of new ulcer eruption, pain scores (VAS), and ulcer size. The Chi-Square test will be employed to compare gender distribution, distribution of RAS on mucosal epithelium, history of drug allergies, and dietary habits. The significance level for statistical tests was set at α = 0.05, with a confidence level of 80% (Ghorbani et al., 2020; Shao and Zhou, 2020).

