## 3 Discussion

Recurrent Aphthous Stomatitis (RAS), also known as recurrent aphthous ulceration (RAU) or commonly referred to as canker sores, is a prevalent condition characterized by recurring circular ulcers that affect the oral mucosal layers. RAS entails inflammation occurring within the oral mucosal layer. This condition often arises due to hormonal changes, physical stress, trauma, alterations in psychological conditions, chemical irritations, and is even associated with allergies and genetic factors. Irritation can manifest in any part of the oral cavity, with a duration ranging from 4 to 14 days (Tarakji et al., 2015). It is recognized as one of the most painful inflammatory ulcerative conditions in the oral cavity, causing discomfort during eating, swallowing, and speaking (Moghadamnia, Motallebnejad and Khanian, 2009).

A range of medications, sourced from natural or synthetic origins, is utilized as treatments for RAS. These therapies exhibit diverse mechanisms of action, encompassing anti-inflammatory, antioxidant, immunomodulatory, analgesic, wound healing, antiulcer, antibacterial, antiviral, and antibiotic effects (Dhama et al., 2018). Alternative therapy for patients with RAS may involve the use of herbal remedies, such as α-mangostin derived from the rind of the mangosteen fruit (*Garcinia mangostana* L.). Several studies indicate that mangosteen peel extract containing α-mangostin exhibits potent antioxidant activity and the ability to promote wound healing. This suggests its potential effectiveness in formulating pharmacologically beneficial agents for wound healing (Fajeriyati, Muchtaridi and Sopyan, 2021).

A rat excision wound model was employed to investigate the effects of α-mangostin on wound healing. According to their findings, topical application of α-mangostin ointment enhanced the wound healing process. Parameters utilized in the experiment included wound closure duration and wound contraction. On the 20th day post-treatment with α-mangostin, a 90% wound healing rate was observed in the treated group. Based on their research, these results affirm that α-mangostin possesses wound healing properties (Sasikala Chinnappan et al., 2020).

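### Section 2.8 ties pain recording to the ulcerative stage, so collection of a primary endpoint can depend on healing; section 2.7 sets no such limit

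*Protocol article*

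**What the plan says.** The article describes pain recording in three places.

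- Section 2.7 (Outcomes): "Ulcer pain score will be measured once a day using Visual Analog Scale (VAS) pain record individually by the participants". It sets no end point and no condition on the ulcer.
- Section 2.8 (Intervention), on materials: "Visual analog scale records and sheets for noting side effects/adverse drug reactions are provided throughout the testing phase".
- Section 2.8, the next sentence, on what participants are told: "Participants are instructed to record pain scores daily during the ulcerative stage".

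The Abstract makes VAS a primary endpoint: "The diameter of ulcer and visual analog scale (VAS) score will be used as the primary efficacy endpoint". It also sets the comparison times: "The outcome measure will be compared between the two arms at the baseline, day 3, day 5, and at the end of 7 days". Section 2.9 names an independent-samples t-test "to compare age, time of new ulcer eruption, pain scores (VAS), and ulcer size". The article does not say whether a participant with a healed ulcer continues to score pain or is entered as 0.

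**The concern.** Taken at its plain meaning, the section 2.8 instruction ends pain recording when the ulcer heals. Healing is something the film is meant to change. Whether a day 5 or day 7 VAS exists would then depend on an effect of treatment, and the participants left in each arm at those visits would no longer be the randomised groups.

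The planned t-test on recorded scores would compare pain among those still ulcerated. That is a different question from whether participants given the film have less pain than those given placebo, and randomisation does not protect the answer. The number contributing also falls, in a trial planned on about 19 evaluable participants per arm.

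**Working it through.** **The plan's own figure.** Section 2.5 gives 19 per arm and 20% withdrawal: 19 / (1 − 0.20) = 23.75, rounded up to 24, as stated. That 20% is an allowance for withdrawal. Section 2.5 mentions no allowance for scores that stop at healing.

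**How many ulcers heal inside the window.** Entry is within 48 h of onset (section 2.4), so ulcer age on day 1 is 0 to 2 days. The Discussion gives RAS lesions "with a duration ranging from 4 to 14 days". Assume durations uniform on that range; then P(healed by age a) = (a − 4) / 10 for a between 4 and 14.

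- Day 3: age 2 to 4 days, so 0%.
- Day 5: age 4 to 6 days, so 0% to 20%, about 10% on average if entry age is uniform over 0 to 2 days.
- Day 7: age 6 to 8 days, so 20% to 40%, about 30% on average.

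These are untreated ulcers. The article gives no human healing rate on the film.

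**Direction of the bias.** Let h be the proportion healed and m the mean VAS while ulcerated, with subscripts A (film) and P (placebo), and take pain as 0 once healed.

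- All randomised: D_all = (1 − h_P)·m_P − (1 − h_A)·m_A
- Recorded scores only: D_rec = m_P − m_A
- Subtracting: D_all − D_rec = h_A·m_A − h_P·m_P

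Dropping healed participants understates the difference when h_A·m_A exceeds h_P·m_P, and overstates it when the inequality is reversed.

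**Size under assumed inputs.** Every healing rate, mean and SD below is an assumption. The differences come from the formulas. The chance of a significant result favouring the film is from simulation with 19 per arm, SD 1.5 and VAS truncated at 0 to 10. Truncation lowers some of the simulated differences by up to about 0.06.

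| Healed P / A | VAS while ulcerated P / A | D_all | D_rec | Chance: healed = 0 | Chance: healed missing |
|---|---|---|---|---|---|
| 20% / 50% | 3 / 3 | 0.8×3 − 0.5×3 = 0.90 | 0 | 34% | 3% |
| 20% / 50% | 3 / 2.5 | 0.8×3 − 0.5×2.5 = 1.15 | 0.5 | 51% | 11% |
| 30% / 40% | 3 / 2 | 0.7×3 − 0.6×2 = 0.90 | 1.0 | 34% | 34% |
| 30% / 30% | 3 / 2 | 0.7×3 − 0.7×2 = 0.70 | 1.0 | 22% | 38% |

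In the first two rows about 15 placebo and 9.5 film participants contribute a score. A further model treats healing as the low end of a single severity scale (latent mean 2, SD 2, film shift 1.82). The difference goes from 1.28 to 0.92 and the chance of significance from 72% to 31%, with about 16 against 10 contributing.

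**The case against.** The strongest reply is that nothing in the article says healed participants leave the analysis. Section 2.7 and the supply of VAS sheets point to collection over the full period, the Abstract commits to comparisons up to day 7, and "ulcerative stage" may be loose wording for the treatment week. How a healed ulcer is scored is also a matter commonly left to an analysis plan, which is not shown here and may enter 0. Assessors measure the ulcer on days 3, 5 and 7 whatever the diary contains, so healing status is known at each comparison visit. Ulcer diameter, the other primary endpoint, is untouched by the diary wording.

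Much of this stands. The loss of healed participants is a consequence of following the instruction and is not a stated rule, and the scores can be partly recovered. What remains is that the article contradicts itself on when a primary outcome is collected, and the narrower version is the one participants are told. An analysis plan can assign a value after healing, but it cannot restore a score that was never recorded, and assigning 0 assumes that pain ends with the ulcer.

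A reader might also infer that the rule must bias the trial towards no effect, with a large and known loss of power. The documents do not support that. The last two rows of the table show the difference enlarged, and the article presents pain relief as a treatment aim in its own right alongside healing.

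**Conclusion.** The point holds as an inconsistency in a stated collection rule for a primary endpoint. If the section 2.8 instruction is followed and recorded scores are analysed as they stand, the day 7 VAS comparison, and to a lesser extent day 5, is made in groups selected by a treatment outcome. Day 3 is essentially unaffected. On the article's entry window and lesion duration, with uniform durations assumed, 20-40% of untreated participants would lack a day 7 score.

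The direction depends on how the film works. A benefit mainly through faster healing would be diluted or lost, and a benefit mainly through less pain while ulcerated could be overstated. If healing is equal in both arms and pain while ulcerated does not differ, there is no bias. The table illustrates the range but does not estimate the bias in this trial.

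**What to change.** Align sections 2.7 and 2.8 so that both say VAS is recorded on all 7 days, whether or not the ulcer is still present, and change the diary instruction to match. Recruitment began in December 2023 and is described as ongoing, so early correction limits the number of scores that are never collected.

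For participants already enrolled whose VAS is missing after an assessor has documented healing at day 3, 5 or 7, score VAS as 0 from that visit. Add a sensitivity analysis, because this assumes that pain ends with the ulcer; full diaries collected after the change would help to test that assumption.

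The cost is a few extra diary entries per participant, one corrected instruction and one scoring rule.

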## 2 Methods

### 2.1 Study design

This is a two-arm, double-blinded, randomized controlled trial scheduled to take place at the Padjadjaran University Dental and Oral Hospital in Bandung, Indonesia. The trial aims to evaluate the efficacy and safety of α-mangostin hydrogel film in comparison to a placebo. Patients diagnosed with RAS will be randomly assigned to one of the two arms, and they will receive the mucoadhesive film for a duration of 7 days. The primary efficacy endpoints will be determined based on the measurement of ulcer diameter and the use of the Visual Analog Scale (VAS) score. These outcome measures will be assessed at various time points, including prior to the initial visit (baseline), on day 3, day 5, and at the conclusion of the 7-day treatment period based on previous trial on 2020 and 2022 (Ghorbani et al., 2020; Molania et al., 2022).

Ethics approval has been obtained from Research Ethics Committee of the Faculty of Medicine, Universitas Padjadjaran, Indonesia (approval reference number: 806/UN6.KEP/EC/2023). The trial was registered in the Clinicaltrials.gov registry (Trial number NCT06039774).

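### Section 2.8 asks participants to record effects tied to the film, while section 2.7 makes adverse events the outcome without a causality condition, so brief unattributed events may go unrecorded

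*Protocol article*

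**What the plan says.** Section 2.1 gives the aim as to "evaluate the efficacy and safety of α-mangostin hydrogel film" against placebo, so safety is a stated purpose of the trial.

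Section 2.7 lists adverse events among the outcomes and says when recording begins: "Adverse events (AEs) will be documented once participants commence drug administration". It then sets out the content: "The AE record will encompass: descriptive analysis, the timing of onset and resolution, severity, frequency, the necessity for treatment", plus details of any treatment given. Attribution to the film is not a condition of entry. The same section adds that vital signs "will be monitored during follow-up visits" and that "participants will also be queried about any discomfort symptoms they may be experiencing".

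Section 2.8 describes what participants themselves do. They are given pain-score records, and "sheets for noting side effects/adverse drug reactions are provided throughout the testing phase". They are instructed "to document any side effects associated with the film usage". Separately, they are told to stop using the film promptly "if rash or oral mucositis appears during the trial and report any occurrences to the supervising physician and researcher". The record sheets are handed in when the study ends; the article does not mention an earlier review of them.

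**The concern.** An adverse event is any untoward occurrence after treatment starts. A side effect or adverse drug reaction is one with a suspected link to the product. Section 2.7 uses the wider term for the outcome, and section 2.8 uses the narrower one for the form that participants fill in. A participant with a headache or an upset stomach who puts it down to something else has no clear instruction to write it down.

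In a randomised, blinded comparison, cause is best judged by recording events regardless of opinion and comparing the arms. If the participant's opinion is applied first, some events may never reach that comparison, and the recorded counts may be too low in either arm. With a planned 24 participants per group, a short list of events could then look somewhat more reassuring than it should.

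**Working it through.** The article gives no figure for event rates or completeness of reporting, so there is nothing to reproduce or recompute. The check is a comparison of the two sections, followed by a check of each route by which an event could reach the record.

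**Step 1: scope of the two instructions.**

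| | Section 2.7 | Section 2.8, participant's record |
|---|---|---|
| Term used | Adverse events | Side effects / adverse drug reactions |
| Link to film required? | None stated | Yes, on the natural reading of "to document any side effects associated with the film usage" |
| Period | From start of treatment | Throughout the testing phase |
| Detail wanted | Onset, resolution, severity, frequency, treatment | Not stated |

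The narrower scope appears twice in section 2.8, once in the name of the sheet and once in the instruction. A single loose word is therefore an unlikely explanation.

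**Step 2: routes that do not depend on the participant's attribution.**

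- *Question about discomfort (section 2.7).* It carries no condition on cause. As worded ("participants will also be queried about any discomfort symptoms they may be experiencing"), it asks about present symptoms and does not clearly reach back to those that have resolved.
- *Vital signs (section 2.7).* These show only what is measurable at the visit.
- *Rash or oral mucositis (section 2.8).* The report is triggered by appearance, whatever the cause, and can be made between visits. It covers two named events.

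**Step 3: interval between visits.** Ulcer size is measured on days 1, 3, 5 and 7. If these are also the visit days (an assumption, since the article does not give a separate visit schedule), the gaps are 3 − 1 = 2, 5 − 3 = 2 and 7 − 5 = 2 days. Recall over two days is short, so a good part of what is missing from the sheet could be recovered if staff ask about the whole interval.

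**Step 4: what remains.** An event can miss every route described if four things hold together: the participant does not attribute it to the film; it is neither rash nor oral mucositis; it resolves before the next visit; and it is not picked up by the question about current discomfort. For such events the sheet is the only same-day source described for the onset, resolution and frequency that section 2.7 asks for.

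**The case against.** The best reply is that the two sections describe complementary sources. Participants note suspected film effects, staff ask about any discomfort, and together these feed an adverse-event record that is nowhere said to be the participant's sheet. The instruction in section 2.8 can also be read as covering whatever happens while the film is in use, with no judgement about cause. The sheet itself is not shown, and a journal article commonly leaves form wording to the full protocol.

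Much of this stands. The sheet is one input to the safety record, and the other routes limit the loss. What does not fall away is that the article states an instruction, and on its natural reading that instruction is narrower than the outcome it serves. This is a mismatch in the text as published, not a detail left out. If the phrase was meant to refer to timing only, its ambiguity is itself a reason to reword it.

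A reader might infer more than the documents support, in three ways:

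- *That section 2.7 promises every adverse event and section 2.8 admits only attributed ones, so that events are certain to be lost.* Section 2.7 does not say all and section 2.8 does not say only. The other capture routes mean that events may be lost, not that they are.
- *That the true event rate can be bounded by scaling up the recorded rate for under-reporting.* That needs a capture fraction. The article gives none, and any assumed value would treat the sheet as the sole source.
- *That the arms are compared unfairly.* Participants are blinded and both arms have the same instructions, and nothing in the text points to a difference in reporting between them.

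**Conclusion.** The point holds as a minor inconsistency. Sections 2.7 and 2.8 set different scopes for safety reporting, and the narrower one leaves a first judgement about cause to the participant. The consequence is a possible gap for transient, unattributed events that resolve before a visit. Its size cannot be derived from the document.

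The conclusion assumes that the instruction in section 2.8 is read in its ordinary sense, that the sheet follows that wording, and that the question at visits is put as written. If the sheet already asks for all events, or staff routinely ask about everything since the last visit, the gap shrinks or disappears and only the sentence needs correcting. The efficacy outcomes are unaffected.

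**What to change.** Reword section 2.8 and the sheet so that participants record any new or worsened symptom or illness since the first film, whatever they think caused it. Have the blinded investigator assess relatedness afterwards. Section 2.6 names participants and outcome assessors as blinded, so the text should make clear that whoever judges relatedness is also unaware of allocation. If the sheet in the full protocol already asks this, correct only the sentence in section 2.8.

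The cost is one sentence and one form, with more trivial entries to review. Section 4 says that recruitment began in December 2023 and is ongoing, so participants already treated will have had the narrower instruction. The date of the change should be recorded so that event counts before and after it can be told apart. The change concerns data collection only and leaves treatment and the instruction to stop the film as they are.
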